#### Exclusion criteria for clinicians

2.2.4

Temporary or part-time staff without direct patient care responsibilities;Participation in conflicting AI-related clinical trials within the past 6 months.

### Interventions

2.3

#### Phase I: model development and internal validation

2.3.1

This phase utilizes retrospective EHRs from 87 hospitals (Table 1) in Jiangsu Province (from January 2019 to December 2024), encompassing four key data categories:

Demographics: age, sex, vaccination history, and comorbidities.Clinical symptoms: fever duration, cough frequency, dyspnea severity, and other symptoms detailed (Table 2).Laboratory/imaging data: viral subtype (confirmed via RT-PCR), blood cell counts, and chest X-ray/computed tomography (CT) findings.Outcomes: severe influenza progression and mortality, defined as intensive care unit (ICU) admission or mechanical ventilation.

**Table 1 tab1:** Datasets distribution.

City	Hospitals
Nanjing	Jiangsu Provincial People’s Hospital, General Hospital of the Eastern Theater Command, Nanjing Drum Tower Hospital, Jiangsu Provincial Hospital of Traditional Chinese Medicine, Zhongda Hospital Affiliated to Southeast University, Nanjing First Hospital, The Second Affiliated Hospital of Nanjing Medical University, Nanjing Hospital of Traditional Chinese Medicine
Wuxi	Wuxi People’s Hospital, The Affiliated Hospital of Jiangnan University, Wuxi Hospital of Traditional Chinese Medicine
Xuzhou	The Affiliated Hospital of Xuzhou Medical University, Xuzhou Central Hospital, Xuzhou First People’s Hospital, Xuzhou Mining Group General Hospital, Xuzhou Hospital of Traditional Chinese Medicine
Changzhou	Changzhou First People’s Hospital, Changzhou Hospital of Traditional Chinese Medicine, The Third Affiliated Hospital of Soochow University (Changzhou Second People’s Hospital)
Suzhou	The First Affiliated Hospital of Soochow University, The Second Affiliated Hospital of Soochow University, Suzhou Municipal Hospital, Suzhou Hospital of Traditional Chinese Medicine
Nantong	The Affiliated Hospital of Nantong University, Nantong First People’s Hospital, Nantong Hospital of Traditional Chinese Medicine
Lianyungang	Lianyungang First People’s Hospital, Lianyungang Hospital of Traditional Chinese Medicine, Lianyungang Second People’s Hospital
Huai’an	Huai’an First People’s Hospital, Huai’an Second People’s Hospital, Huai’an Hospital of Traditional Chinese Medicine
Yancheng	Yancheng First People’s Hospital, Yancheng Hospital of Traditional Chinese Medicine, Yancheng Third People’s Hospital
Yangzhou	Subei People’s Hospital, Yangzhou First People’s Hospital, Yangzhou Hospital of Traditional Chinese Medicine
Zhenjiang	The Affiliated Hospital of Jiangsu University, Zhenjiang First People’s Hospital, Zhenjiang Hospital of Traditional Chinese Medicine
Taizhou	Taizhou People’s Hospital, Taizhou Hospital of Traditional Chinese Medicine, Taixing People’s Hospital
Suqian	Suqian People’s Hospital, Suqian Hospital of Traditional Chinese Medicine

**Table 2 tab2:** Data collection framework.

Category	Specific data items	Collection tool
Demographics	Age, sex, contact details, vaccination history, comorbidities	EHR extraction
Symptoms	Fever (duration, max temperature), cough (frequency, sputum), dyspnea, headache, nausea/vomiting	Structured EHR forms + Patient diaries
Medical History	Previous influenza episodes, chronic diseases (type, duration), vaccination details	EHR extraction + Clinician interview
Laboratory/Imaging	Viral subtype (RT-PCR), blood counts, chest X-ray/CT findings	Lab/radiology reports
Treatment	Antiviral drugs (name, dosage), hospitalization duration, ICU admission	EHR extraction + Pharmacy records
Outcomes	Severe influenza progression (yes/no), recovery time, mortality	Adjudication panel review

We plan to divide the collected data into an 80% training subset and a 20% internal validation subset. When building the model, we will progressively stratify by hospital, influenza season, and high-risk subgroup characteristics, so that the initial model built may have a balanced representation. We plan to build a preliminary severe influenza model using the deep neural network model of ResNet-50 (21). The metrics we predesigned to assess the baseline performance of the model were area under the curve (AUC) and sensitivity. Whereas the complex technical parameters of these will be published in the final version of the research results, in this research protocol we focused more on the deployment of the clinical research programme. This is more beneficial for clinicians or influenza patients to read and disseminate.

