#### Rationale for multi-center design

2.1.2

The principle of the multicentre design is based on a statistically full sample size as a reference basis. In other words, we included all hospitals in Jiangsu Province that met the study eligibility criteria. This design allows for the establishment of model performance in different Jiangsu regions and in different clinical settings, and ensures general applicability from the statistical principle. Considering the perspective of urban and rural stratification, healthcare resources are generally richer in cities than in rural areas, and we designed it in this way to precisely address healthcare inequality under the geographic factor. [name] concluded that influenza outbreaks have a seasonal element, and the peaks of outbreaks in the northern part of Jiangsu are different from those in the southern part of Jiangsu. This design in a full sample size perspective provides a natural experimental platform for assessing influenza disease observations with seasonal fluctuations. We ensure that the accuracy of the diagnosis will not be affected by the transmission factors of resource differences and geographical differences.

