#### Data collection timeline

2.7.2

The study’s data collection is structured into two distinct phases: retrospective (Phases I–II) and prospective (Phases III–V).

During the retrospective phase, EHRs data spanning 2019 to 2024 will be extracted from all 87 participating hospitals via institution-specific application programming interfaces (APIs), with completion targeted within 6 months to ensure timely progression to subsequent stages.

In the prospective phase, real-time data collection will occur throughout the 2025 influenza season, capturing clinical, diagnostic, and outcome variables as they emerge. These data will be synchronized daily to a centralized, secure database to maintain continuity and enable immediate analysis.

This phased approach balances historical insights with dynamic, real-world validation, ensuring comprehensive evaluation of the AI model across diverse temporal and operational contexts.

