#### Primary outcome analysis

2.8.1

The AUC will serve as the primary metric to evaluate the diagnostic accuracy of the AI model. To account for variability inherent in multi-reader, multi-case study designs, the DBM method will be employed, which adjusts for differences in clinician interpretations and case complexity. Analyses will be conducted using the MRMCaov (v0.2.1) and pROC (v1.18.0) packages in R, generating AUC values with 95% confidence intervals (CIs) derived from non-parametric bootstrapping (1,000 iterations). A clinically significant improvement is predefined as a ΔAUC more than 0.15 between the model-assisted and control groups, with the null hypothesis assuming no discriminative capacity (AUC less than 0.70, equivalent to random guessing). This approach ensures robust statistical inference while addressing real-world diagnostic variability across clinicians and settings. Hyperparameter optimization was conducted via Bayesian optimization with 5-fold cross-validation, prioritizing AUC on the validation set.

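### Phase II is called external validation but draws on the same 87 hospitals and 2019–2024 extraction as model development, so it is at best internal, and no phase tests the model in an unseen hospital

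*Protocol article*

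**What the plan says.** All references are to the protocol article.

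- **Development data** (2.3.1, Phase I): "This phase utilizes retrospective EHRs from 87 hospitals (Table 1) in Jiangsu Province (from January 2019 to December 2024".
- **Split** (2.3.1): "We plan to divide the collected data into an 80% training subset and a 20% internal validation subset". In building the model, "we will progressively stratify by hospital, influenza season, and high-risk subgroup characteristics".
- **Grouping of phases** (2.7.2, Data collection timeline): the phases are "retrospective (Phases I–II) and prospective (Phases III–V"; for the first group, "EHRs data spanning 2019 to 2024 will be extracted from all 87 participating hospitals".
- **Choice of hospitals** (2.1.2, Rationale for multi-center design): "we included all hospitals in Jiangsu Province that met the study eligibility criteria".
- **Label**: the abstract's Methods, the phase overview (2.1.4) and the heading of 2.3.2 all call the second phase external validation. Section 2.3.2 names no separate hospitals, dates or reserved subset for the cases that clinicians judge.
- **Calibration** (2.3.3, Phase III): the models used in Phase III are said to have been calibrated during Phase II.
- **Tuning** (2.8.1, Primary outcome analysis): "Hyperparameter optimization was conducted via Bayesian optimization with 5-fold cross-validation, prioritizing AUC on the validation set".
- **Later data** (2.3.5 and 2.7.2): Phases III–V collect data in the 2025 season. Phase V runs in all 87 hospitals.

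**The concern.** External validation means testing a fixed model on data from a setting or period that played no part in building it. Phase II shares its hospitals, years and extraction with model development, and the model is adjusted in that same phase. A result reported from it as external would describe performance in hospitals whose patients, coding habits, laboratories and case mix the model may already have learned.

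This matters because of what the protocol claims. The introduction faults earlier AI models for lacking external validation across regions and levels of healthcare resource. It then hypothesises robustness across hospitals with differing resources, and section 2.1.2 claims general applicability. A reader would look to Phase II for the evidence and would not find it there.

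A second, smaller question concerns the Phase I internal estimate. If the subset on which the AUC is reported is also the one on which hyperparameters are chosen, that AUC is biased upwards.

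**Working it through.** The protocol states no figure to reproduce here. The check traces the data through the phases and then sizes the tuning question under stated assumptions.

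**1. What remains for Phase II after the split (2.3.1)**

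100% collected − 80% training − 20% internal validation = 0%.

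Phase II cases taken from the stated extraction therefore lie in the training subset or in the internal validation subset.

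**2. Hospitals and years by phase**

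| Phase | Hospitals | Period | New hospitals | New period |
|---|---|---|---|---|
| I, development (2.3.1) | 87 | 2019–2024 | – | – |
| II, labelled external (2.3.2, 2.7.2) | the same 87 | 2019–2024 | 0 of 87 | none of the 6 years |
| III–IV (2.7.2) | none described as new | 2025 | none described | yes |
| V (2.3.5) | the same 87 | 2025 | 0 of 87 | yes |

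Section 2.1.2 says every eligible hospital in the province is already included, so none is in reserve.

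**3. Independence of Phase II from fitting**

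Section 2.3.3 has the model calibrated in Phase II. Data used to calibrate a model cannot also give an independent estimate of its calibration.

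**4. Which set is used for tuning (2.8.1)**

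- Reading A: the validation set is the 20% subset, the only validation set that the article defines. Selection and reporting then use the same data.
- Reading B: it is the held-out fold of the 5-fold cross-validation inside the 80%. The 20% subset then gives a fair internal estimate for these hospitals.

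The wording allows both.

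**5. Size of the optimism under Reading A (illustrative)**

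The document does not give the inputs. Assumed: true AUC A = 0.85; share of severe cases 10–30%; K = 20–50 equally good configurations; correlation ρ = 0.80–0.95 between their AUC estimates. Two sizes of the 20% subset follow from figures in the article:

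- 0.20 × 348 ≈ 70, from the total enrolment in 2.5.3;
- 0.20 × 87 × 100 = 1,740, from the hospital minimum in 2.1.1.

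The standard error is the Hanley–McNeil formula with n₁ severe and n₀ non-severe cases:

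SE² = [A(1−A) + (n₁−1)(a−A²) + (n₀−1)(b−A²)] / (n₁n₀), where a = A/(2−A) and b = 2A²/(1+A).

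Optimism ≈ SE × √(1−ρ) × m, where m is the expected maximum of K independent standard normal values (about 1.87 for K = 20 and 2.25 for K = 50).

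| Subset size | Severe share | SE | ρ, K | Optimism in AUC |
|---|---|---|---|---|
| 70 | 10% | 0.0935 | 0.80, 50 | 0.094 |
| 70 | 30% | 0.0564 | 0.95, 20 | 0.024 |
| 1,740 | 10% | 0.0186 | 0.80, 50 | 0.019 |
| 1,740 | 30% | 0.0112 | 0.95, 20 | 0.005 |

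For example, the first row is 0.0935 × √0.20 × 2.25 ≈ 0.094. The range is about 0.02 to 0.09 for the small subset and 0.005 to 0.02 for the larger one.

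**The case against.** The strongest reply is that much of the harm a reader might infer is not in the text. Five such inferences go too far.

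- **That Phase II reuses the records on which the model was fitted.** The documents show a shared source pool, not shared records. The cases could come from the 20% subset. That would be sounder than reusing training records, but still internal.
- **That tuning on the reported subset is established.** Reading B is permissible, so this is an ambiguity to resolve, not a demonstrated bias.
- **That the optimism feeds into the 0.85 used for the sample size.** Section 2.5.1 takes that value from a cited source, so nothing in Phases I–II can affect it.
- **That a miscalibrated model is carried forward.** Optimism is bias in a performance estimate. It does not show miscalibration.
- **That robustness goes untested altogether.** Phases III–V use 2025 data, and urban/rural and north/south subgroups are prespecified in 2.4.3 and 2.8.3. Only testing in unseen hospitals is missing.

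Two further points on the other side carry some weight. The legend of Figure 1 mentions internal and external validation steps, so the partition may be drawn there; the figure was not available for this review. The stratification sentence refers to building the model and not expressly to the 80/20 split, so it does not prove that every hospital and season is in the training subset. The introduction's list of stages, which names internal but no external validation, is weak evidence either way because it also omits the multi-reader phase.

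It could also be said that a journal article condenses the full protocol. But this article states the hospitals, years, split and grouping of phases, and together these leave nothing external. Table 1 is cited for 87 hospitals and lists 46; nothing says that the other 41 are held out.

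**Conclusion.** The concern holds in this form. Phase II, as described, has no external hospital and no external period: 0 of 87 hospitals and 0 of 6 calendar years lie outside the development data, and 0% of the extraction is reserved. It is at best internal validation, and the calibration step in that phase weakens it further. Validation over time exists in the 2025 phases, so the gap is specific: no phase is described as testing the model in a hospital it has not learned from, and the plan does not support a claim of transportability to such hospitals.

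This conclusion rests on the text of 2.3.1 and 2.7.2 and on no numerical assumption. It would change only if the full protocol or Figure 1 defines a held-out set of hospitals or a held-out period.

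The tuning point is conditional. Under Reading A the Phase I validation AUC is optimistic, by about 0.005 to 0.09 on the assumed inputs. Under Reading B this source of optimism is absent.

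**What to change.** 1. **Reserve whole hospitals before training.** Choose them to cover north and south Jiangsu and urban and rural facilities. Use none of their records for training, tuning, calibration or fitting the imputation models. Make them the Phase II set, and calibrate on development data only. As an illustration, 20% of 87 is 17.4, so about 17 hospitals.
2. **If that is not acceptable, relabel.** Call Phase II internal validation throughout and withdraw the external-validation claim. Describe Phase V as temporal validation in the same hospitals.
3. **State the tuning rule.** Hyperparameters are chosen only by 5-fold cross-validation inside the 80%, and the 20% subset is scored once, after the model is fixed.

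None of these needs new data. With about 20% of records set aside under option 1 (assuming hospitals of similar size), the training share falls from 80% to 0.80 × 0.80 = 64% of all records, one fifth fewer. The reported AUC will probably be lower. Timing matters: section 2.8.1 reports tuning in the past tense. If the model has already been fitted on all hospitals, option 1 requires refitting without the reserved ones; option 2 needs only a change of text.

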#### Final allocation

2.5.3

The study will enroll a total of 348 patients, comprising both retrospective cohorts (historical data from 2019 to 2024) and prospective cohorts (real-time data from the 2025 influenza season). Clinician participation includes 218 practitioners, stratified by hospital tier (urban vs. rural) and seniority level (resident, attending, or chief physician) to ensure balanced representation of clinical expertise and institutional resource variability. This allocation strategy optimizes statistical power while reflecting real-world healthcare diversity, supporting robust validation of the AI model across heterogeneous settings.

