#### Intervention groups

2.6.3

In the control group, clinicians (without any AI assistance) will diagnose influenza cases using standard clinical protocols, integrating symptoms, laboratory results, and imaging findings. Patients in this group will receive routine care based solely on clinician assessments.

In contrast, the model-assisted group will utilize a secure digital dashboard providing real-time AI predictions, including a risk score (0–100%) for severe influenza progression and highlighted contributing factors (such as prolonged fever duration, abnormal lymphocyte counts).

While the model offers data-driven insights, its outputs are non-prescriptive; clinicians retain full authority to accept, modify, or reject recommendations, ensuring clinical judgment remains central to decision-making. This design balances technological support with practitioner autonomy, reflecting real-world diagnostic workflows.

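### The only model type planned, ResNet-50, is an image network, but every listed input is tabular or report-derived, and no phase would show a loss against a simpler model

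*Protocol article*

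**What the plan says.** **Model.** Section 2.3.1: "We plan to build a preliminary severe influenza model using the deep neural network model of ResNet-50 (21"). No other model type appears in the article. The same section leaves technical parameters to the results publication.

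**Inputs.** Section 2.3.1 lists "Demographics: age, sex, vaccination history, and comorbidities", then "fever duration, cough frequency, dyspnea severity, and other symptoms detailed" in Table 2, then "viral subtype (confirmed via RT-PCR), blood cell counts, and chest X-ray/computed tomography (CT) findings". Table 2 repeats the last group as "Viral subtype (RT-PCR), blood counts, chest X-ray/CT findings" and gives the collection tool as "Lab/radiology reports". The data item of the framework in the Introduction names clinical, laboratory and demographic features and does not mention images.

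**Output.** Section 2.6.3 has the dashboard show a risk score and "highlighted contributing factors (such as prolonged fever duration, abnormal lymphocyte counts").

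**Checks on the model.** Phase I uses AUC and sensitivity (2.3.1), with no reference model and no pass mark. Section 2.8.1 tunes hyperparameters by Bayesian optimisation with 5-fold cross-validation. Phases II to IV set AI-assisted clinicians, or the model, against clinicians without it (2.1.4, 2.3.2 to 2.3.4).

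**The concern.** A convolutional network gains its advantage from spatial structure: neighbouring pixels carry related information. Age, fever duration, comorbidity and lymphocyte count have no such order. The article gives no reason to use an image architecture for them and does not say how they would be fed into one. As written, the model type does not fit the data described.

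The choice carries through the programme. The Phase I model supports the clinicians in Phase II, is calibrated there for Phase III, and an AI model is used in the Phase IV trial and deployed in Phase V. If a simpler model on the same inputs discriminates better, the assisted arm works with a weaker tool than the data allow. A shortfall in Phase IV could then be read as a failure of AI assistance when the cause was the choice of model.

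**Working it through.** This is mainly a reading check; the only arithmetic concerns the margin and the training-set size.

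**1. Are the inputs tabular or pixels?**

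| Section | What it implies |
|---|---|
| Introduction, framework list | clinical, laboratory and demographic features; no images |
| 2.3.1, data categories | imaging enters as findings |
| 2.3.1, Table 2 | findings come from reports |
| 2.3.5 | the deployed model analyses EHRs |
| 2.6.3 | example explanatory factors are a symptom duration and a blood count |
| 2.7.4, 2.8.4 | missing values are handled as continuous variables (MICE) and categorical variables (mode imputation) |
| 2.8.5 | stability is the variation in AUC across imputed datasets |
| 2.7.3 | imaging files are named, but as source documents for auditing records |

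The imputation and stability plans are written for table columns. No section makes raw images a model input.

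**2. Which phase could reveal a poor choice of model?**

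- Phase I: AUC and sensitivity of the one model. A very low value would be seen, but there is nothing to compare a moderate value with.
- Tuning (2.8.1): settings within the model type, not a choice between types.
- Phases II to IV: the comparator is the unassisted clinician.
- Phase V: model against adjudicated outcome, and clinician diagnosis before and after seeing the model.

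No phase contains a second model, so a loss relative to one cannot be seen.

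**3. What would a loss do to the primary criterion?** Inputs from 2.5.1: assisted AUC 0.85, clinician-only AUC 0.70. Criterion from 2.3.4 and 2.8.1: ΔAUC above 0.15.

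- Planned difference: 0.85 − 0.70 = 0.15, equal to the criterion.
- If the model choice costs L in assisted AUC, the expected difference is 0.15 − L, below the criterion for any L > 0.

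The article gives no basis for a value of L. Because clinicians may override the model, L need not equal the loss in the model's own AUC.

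**4. Does the training-set size settle the matter?** Section 2.5.3 says "The study will enroll a total of 348 patients, comprising both retrospective cohorts" and prospective ones. On that reading the 80% training share is at most 0.8 × 348 = 278 patients. Section 2.1.1 asks each hospital for at least 100 laboratory-diagnosed patients; with 87 hospitals that is at least 87 × 100 = 8,700, and 0.8 × 8,700 = 6,960. The article does not decide between these, and the mismatch in step 1 is the same under both.

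**The case against.** - **The text is tentative.** It says plan and preliminary, later sections speak of AI models in the plural, and calibration and tuning follow. This stands: a reader might infer that the architecture is irrevocably fixed, and the article does not say so. It does, however, give no alternative and no step for choosing one.
- **Images may be available.** Section 2.7.3 mentions imaging files, and the factors in 2.6.3 are only examples. This stands against any claim that no images are collected. It does not make images model inputs, since 2.7.3 uses the files to audit records.
- **A bad model would be noticed.** This is true of a grossly poor one, which Phases I and II would expose before randomisation. It is not true of a model that is only worse than a simpler one.
- **A missing benchmark is an omission in a condensed article.** Taken alone, that would be so. The point rests on the stated architecture set against the stated inputs; the benchmark is the remedy. The deferral in 2.3.1 covers technical parameters, and the model type is stated, not deferred.
- **The trial tests assistance against no assistance, not deep learning against regression.** This is correct. One might infer that the randomised comparison is biased; it is not. A weaker model reduces the effect of the intervention under test without making the comparison invalid.
- **The network is not shown to be too large.** This is also correct. With a training set anywhere from 278 to 6,960 or more, the article cannot support that reading.

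**Conclusion.** The mismatch between model type and listed inputs stands, as a point that should be corrected before Phase II but does not invalidate the design. It rests on two things: that ResNet-50 is a convolutional image network, which is general methods knowledge (the article calls it only a deep neural network), and that the inputs are those listed. If raw X-ray or CT images are in fact inputs, the mismatch narrows to how the tabular items are combined with them.

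No AUC loss can be quantified. What the article's figures do show is that the assumed effect leaves no room above the 0.15 criterion to absorb one. The documents support neither the conclusion that the model will perform badly nor the conclusion that a simpler model will do better; they show that the plan as described could not tell.

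**What to change.** In 2.3.1, before Phase II begins:

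1. State whether raw chest X-ray/CT images are model inputs, and if so how they are combined with the tabular items.
2. If they are not, replace ResNet-50 with a model suited to tabular data.
3. In either case, fit a penalised logistic regression and gradient-boosted trees on the same inputs, with the same 80/20 split and the same 5-fold cross-validation. Report the AUC of every model.
4. Set the selection rule in advance: carry forward the model with the best cross-validated AUC, or the simpler one if it lies within one standard error of the best.

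This takes a paragraph of text and a little more analysis on data already planned. It needs no new patients and no change to the randomised phase. The downside is that the model carried forward may not be a deep network, in which case the deep-learning wording in the aim would need softening.
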